#### Weight

Upon admission, caregivers receive instructions from their assigned Equip medical provider on proper procedure for checking weight. Weights are taken in the morning, after voiding, prior to any oral intake and patients are asked to wear light clothing. The patient’s weight (in pounds) is taken twice weekly by caregivers and communicated via text message from caregivers to Equip’s Health Insurance Portability and Accountability Act–compliant medical record platform. For each patient, the RD calculates a target weight for weight restoration. Target weight is calculated using expected weight data from each patient’s CDC BMI-for-age Growth Charts. Our primary end point of interest is weight change during the first 8 weeks of treatment, which will include an average weekly rate of weight gain and total weight change from admission to treatment week 8.

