**Objective:**

Our objective is to compare the effectiveness and acceptability of 2 digitally delivered dietary interventions frequently used in eating disorder treatment settings: (1) calorie-based meal plans and (2) the Plate-by-Plate approach. Specifically, we will explore any potential differences in weight restoration achieved over 8 weeks of treatment as a primary measure of effectiveness, as well as additional treatment outcomes (ED symptoms, anxiety, depression, caregiver burden, and perceived effectiveness and acceptability for both caregivers and clinicians).

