This feasibility study will compare the acceptability of 2 digitally delivered dietary interventions and preliminary effectiveness in early stages of treatment: (1) calorie-based meal plans and (2) the Plate-by-Plate approach [24]. Our primary outcome of interest is weight restoration achieved after 8 weeks of treatment, as this is the best predictor of remission. We will also examine the following treatment outcomes by intervention: ED symptoms, anxiety, depression, caregiver burden and self-efficacy, and caregiver’s acceptability and perception of effectiveness. Acceptability and perceived effectiveness will also be measured for clinicians once week 8 outcomes have been captured for all participants. While we are most interested in early treatment response, patients will be followed and clinical outcomes for patients and caregivers reported throughout the entirety of their treatment course as part of standard practice. We anticipate that the findings from this study will help us better understand the needs and experiences of caregivers undergoing FBT and ultimately, whether 1 approach is superior in terms of influence on treatment outcomes. We will also gain insight around commonly held assumptions, such as the running hypothesis that providing caregivers with a calorie target may undermine parental empowerment and self-efficacy. This study will add to existing FBT literature by exploring the impact of dietary interventions that guide caregivers' process for renourishing their child, for which there is currently no research.

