### Statistical Analysis

The treatment outcomes will be collected via our Health Insurance Portability and Accountability Act–compliant medical record platform and will be extracted by trained research personnel. Descriptive statistics will be used to describe patient characteristics and demographics of our patients and treatment outcomes defined in Table 1. To examine any differences in effectiveness between the 2 interventions, we will compare the rate of weight change between the groups using generalized linear models in R version 4.1.1 (R Core Team). We will also look at outcomes across ED subtypes.

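### The primary outcome is named weight restoration but defined as absolute weight change, without the individual target weight that would measure restoration

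*Protocol article*

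**What the plan says.** Two sections name the primary outcome as restoration. The Abstract's Objective speaks of "differences in weight restoration achieved over 8 weeks of treatment as a primary measure of effectiveness". The last paragraph of the Introduction (under Dietary Interventions) says "Our primary outcome of interest is weight restoration achieved after 8 weeks of treatment".

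The Methods define something else. Table 1 lists the primary outcome as weight change between baseline and week 8. The Weight section says "Our primary end point of interest is weight change during the first 8 weeks of treatment". It names two summaries of that change: a mean gain per week, and the overall difference between admission and week 8. The unit comes from the same section: "weight (in pounds) is taken twice weekly by caregivers". The Statistical Analysis section will "compare the rate of weight change between the groups using generalized linear models".

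The Weight section also states "For each patient, the RD calculates a target weight for weight restoration", derived from growth charts of BMI for age. That target appears in no endpoint, in no row of Table 1 and not in the Statistical Analysis section.

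**The concern.** Restoration means progress toward where a patient ought to be, whereas pounds gained is an absolute quantity. The two would be nearly interchangeable if patients were of similar size and had similar deficits, but the entry criteria do not ensure this. The Participants section admits ages 6 to 24, two diagnoses, and any apparent need for weight restoration, with no minimum deficit stated. The Demographics section reports an average age of 15 and a mix of 84% AN (66% + 18%) and 16% ARFID.

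What is at stake is mainly interpretation. The Significance section hopes to identify a preferred approach for early treatment. A mean difference in pounds would show which arm gained more weight. It would not show how far either arm moved its patients toward their targets, although the patient-level figure needed for that is already calculated. A second, smaller stake is precision: if gain in pounds depends on body size or deficit, that variation sits in the error term unless the model accounts for it.

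**Working it through.** The article gives no alpha, power, effect size or standard deviation, so there is no figure of the plan's own to reproduce. The check has two parts.

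**1. Do equal pounds mean equal restoration?**

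Inputs: 2 lb per week (Procedures, in the description of the calorie-based arm) and 8 weeks (Weight section). The article reports no body weights, targets or deficits, so those below are assumptions. The 2 lb rate is used only as a convenient size of gain from the document.

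Gain over the period: 2 × 8 = 16 lb.

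Gain as percent of target = 100 × 16 / target:

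| Assumed target (lb) | 16 lb as % of target |
|---|---|
| 45 | 36% |
| 60 | 27% |
| 90 | 18% |
| 120 | 13% |
| 140 | 11% |

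Share of the admission deficit closed = 100 × 16 / deficit:

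| Assumed deficit (lb) | Share closed by 16 lb |
|---|---|
| 8 | 200% |
| 16 | 100% |
| 32 | 50% |

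The same entry in the primary analysis can therefore stand for overshooting the target, reaching it, or getting halfway. Replacing total change by an average weekly rate does not help, because the rate is also in absolute units.

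**2. What could adjustment be worth?**

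Inputs: 50 patients per arm (Demographics). Assumed: two-sided alpha 0.05, 80% power, and a correlation r between weight change and the baseline covariates taken together.

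Residual variance = (1 − r²) × unadjusted variance. Equivalent unadjusted total = 100 / (1 − r²). Detectable difference in SD units = (1.96 + 0.84) × √(2/50) × √(1 − r²).

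| r (assumed) | Variance removed | Equivalent unadjusted N | Detectable difference | Power for 0.5 SD |
|---|---|---|---|---|
| 0 | 0% | 100 | 0.56 SD | 71% |
| 0.3 | 9% | 110 | 0.53 SD | 75% |
| 0.5 | 25% | 133 | 0.49 SD | 82% |

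The whole table depends on r, for which the document gives no value. It shows a gain only if the planned model would otherwise leave these covariates out.

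**The case against.** The best defence is that absolute gain fits the protocol's own reasoning. The Abstract's Background and the Introduction justify the outcome by early weight gain as a predictor of remission, and the weekly goal under Procedures is itself in pounds. Measured weight also needs no clinical judgement, whereas the target is set by the RD who delivers the assigned approach. These arguments stand. They are good reasons to keep weight change as the primary measure and not to replace it outright. They do not make pounds a measure of restoration.

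A reader might go further than the documents allow in four ways:

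- **That the comparison is unadjusted.** The Statistical Analysis section names no covariates but excludes none. Generalized linear models can carry them, and the list may sit in an analysis plan that is not shown.
- **That randomisation is unstratified.** Group Assignment mentions a block design and is silent on strata. A condensed article often omits these, so no finding follows.
- **That raw pounds bias the comparison.** Allocation is random. Chance imbalance in size is part of sampling error, which the standard error reflects.
- **That a definite amount of precision is lost.** The equivalent sample of 110 to 133 rests wholly on assumed correlations, and at r = 0 the gain is nil. Nor is percent of target certain to be more precise than pounds.

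Pooling of diagnoses is also partly addressed, since the Statistical Analysis section plans to look at outcomes across ED subtypes.

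**Conclusion.** The mismatch is in the text and is not a gap that an analysis plan would fill. The outcome is named as restoration, then affirmatively defined and analysed as absolute weight change, and the individual target set for restoration goes unused. As defined, the trial can estimate a difference in weight gained without bias from this source, but it cannot say how much restoration each approach achieved.

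The size of the interpretive gap is illustrated by 16 lb being 36% of an assumed 45-lb target and 11% of an assumed 140-lb target. The spread among the enrolled patients is not reported and may be narrower. The precision element is only a possibility: between nothing and about a quarter of the variance for assumed correlations from 0 to 0.5, and only if the model would otherwise be unadjusted.

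**What to change.** 1. Keep weight change in pounds as the primary measure, and call it weight gain in the Objective and Introduction as well as in the Methods.
2. Add a prespecified key analysis of percent of target weight at week 8, adjusted for baseline percent of target.
3. For that analysis, fix the target at its admission value, or recompute it from the growth charts without knowledge of arm. The article does not say whether the target is set before assignment is known or revised later. The second option is therefore the safer one wherever the RD knew the arm when setting the target.
4. State that the weight-change model adjusts for baseline weight, age, sex and diagnosis.

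No new data collection is needed. Age, biological sex, diagnosis and height are extracted from the record (Assessments and Measures, Overview), baseline weight is in Table 1, and the target is already calculated. The cost is wording, a few degrees of freedom with 100 patients, and the work of freezing or recomputing the target.

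Timing needs care. The article was published on 26 January 2023, and analyses were due to be completed that month. The additions should be recorded as prespecified only if they are fixed before outcomes are examined by arm. Otherwise they should be reported as added later. Leaving the primary measure in place avoids the appearance of an endpoint switch.

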#### Eating Disorder Examination Questionnaire Short Form

The Eating Disorder Examination Questionnaire Short Form is an abbreviated 12-item version of the 28-item Eating Disorder Examination Questionnaire survey. The Eating Disorder Examination Questionnaire Short Form is a well-validated and reliable measure, which assesses ED symptom severity. Scores range from 0 to 36, with higher scores suggesting increasing severity of ED behavior [25].

#### Patient Health Questionnaire

The Patient Health Questionnaire-9 is a brief, well-validated, and reliable diagnostic tool for depression. Patients are asked to rate 9 items pertaining to depression symptoms they have found bothersome over the last 2 weeks from “0” (not at all) to “3” (nearly every day). Higher scores indicate greater levels of depression [26].

#### Generalized Anxiety Disorder Scale

The Generalized Anxiety Disorder Scale is a widely used, validated, and reliable self-report tool for screening, diagnosing, and assessing the severity of an anxiety disorder. Patients are asked to rate 7 items pertaining to anxiety symptoms, which are scored from 0 to 3, and the score is totaled. Higher scores indicate increasing severity of anxiety [27].

#### Burden Assessment Scale

The Burden Assessment Scale is a 19-item validated questionnaire that focuses on specific objective and subjective caregiver consequences of individuals with mental illness. Ten items assess objective burden (eg, financial problems) and 9 items assess subjective aspects of burden (eg, feelings and attitudes). Caregivers were asked to indicate the extent to which they experienced the described problem on a 4-point scale, with higher scores indicating greater levels of caregiver burden [28,29].

#### Parent versus Eating Disorders

Parental self-efficacy will be assessed with the Parent versus Eating Disorders, which was adapted from the Parent Versus Anorexia scale. The Parent versus Eating Disorders was designed to capture caregivers’ belief in their ability to overcome their loved one’s eating disorder. Seven items are ranked on a 5-point scale with higher scores indicating greater self-efficacy [30].

#### Caregiver Semistructured Interviews

A semistructured interview (Multimedia Appendix 2) will be completed with caregivers to assess their experience with the assigned renourishment strategy. Caregivers will be contacted directly by a member of the research team via their preferred email address to schedule and the interviews will be conducted via phone. If the caregiver does not respond to contact efforts, a Health Insurance Portability and Accountability Act–compliant Google Forms link will be provided via preferred email through which the caregiver can answer the interview questions, after which efforts to reach the caregiver will be discontinued.

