**Methods:**

Patients (N=100) with either AN or avoidant restrictive food intake disorders (ARFID) aged 6-24 years seeking treatment at a nationwide virtual eating disorder treatment program, were enrolled between May and August 2022. Upon admission, patients were randomly assigned to receive either the calorie-based intervention or Plate-by-Plate approach from their registered dietitian, all of whom have received training as study interventionists. While we were primarily interested in responses during the first 8 weeks of treatment, patients will be followed for up to 12 months. Descriptive statistics were used to describe patient characteristics and demographics. Weight changes and other treatment outcomes between groups will be compared using generalized linear models. Semistructured caregiver and clinician interview transcripts will undergo qualitative analysis.

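### The caregiver acceptability interview is sought by email only, its fallback goes to the same email address, and contact then ends, although the same caregivers already text the clinic's platform twice a week

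*Protocol article*

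**What the plan says.** The contact rule is in Methods, Caregiver Semistructured Interviews. The first step is an email: "Caregivers will be contacted directly by a member of the research team via their preferred email address to schedule". The intended mode is live: "the interviews will be conducted via phone". The fallback is triggered as follows: "If the caregiver does not respond to contact efforts". A "Google Forms link will be provided via preferred email through which the caregiver can answer the interview questions", and after that no further attempt is made.

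Three other places bear on the rule:
- The Objective in the Abstract is to "compare the effectiveness and acceptability of 2 digitally delivered dietary interventions". Table 1 lists the caregiver interview, at about treatment week 8, as a secondary outcome for acceptability and perceived effectiveness.
- The Abstract's Methods say how the interviews will be used: "Semistructured caregiver and clinician interview transcripts will undergo qualitative analysis".
- The Weight section shows a second channel in regular use with the same families. The patient's weight "is taken twice weekly by caregivers and communicated via text message" to the clinic's record platform. Training and Fidelity also lists chat communications among the records reviewed weekly.

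**The concern.** A caregiver who has not answered email is given one more chance, by email. The rule names no other route before contact ends, though the trial depends on text messages from these caregivers for its primary outcome.

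Whether a caregiver responds is settled after randomisation, at about week 8, and may depend on how well the assigned approach is working at home. Randomisation does not balance it between arms. If families who find the approach hard are also slower to answer, the acceptability evidence will come mainly from families who are coping. If that pattern differs between arms, the comparison of the two approaches is affected as well.

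The rule also ties the mode of data collection to responsiveness: a semistructured phone interview for those who reply, a self-completed form for those who do not. The planned analysis speaks of transcripts, which a form does not produce, so the article does not say how the two kinds of answer come together.

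**Working it through.** There is no stated figure to reproduce. The article gives no expected response rate for the interview. The check is therefore a comparison of the sections, with algebra to show what would be needed to size the effect.

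**1. Is the email-only reading correct?** Invitation: preferred email. Interview: phone, once scheduled. Fallback: form link, preferred email. End: no further efforts. No other channel is named, and nothing elsewhere in the article contradicts this.

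**2. Is there another caregiver measure of acceptability?** In Table 1 the caregiver scales are the Burden Assessment Scale (burnout) and Parent versus Eating Disorders (self-efficacy). Neither measures acceptability of the dietary approach. The clinician interview does, but from the dietitians who deliver both approaches. The caregiver interview is the only caregiver source.

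**3. Is another channel available?** Weights arrive by caregiver text twice weekly. Over 8 weeks that is 2 × 8 = 16 expected messages per family, so the channel is in routine use during the weeks before the interview.

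**4. How many families are at stake?** The Results give 50 patients per arm. Assuming one caregiver interview per patient, each family without an answer removes 1/50 = 2% of an arm. ARFID is 16% of 100, so 16 families over both arms. The Participant Selection section looks to caregiver insight for this subgroup, so a few silent families there would matter more.

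**5. Can the bias be sized?** Suppose acceptability were summarised as a proportion. In one arm, let p be the share who answer by phone or form, and let m_R and m_N be acceptability among those who answer and those who do not. The respondents' figure differs from the whole arm's by (1 − p) × (m_R − m_N). The documents give none of p, m_R or m_N, in either arm, and do not plan a proportion at all. Neither size nor sign follows.

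**6. Would comparing arms separately by phone and form help?** Let acceptability be a among responsive families and b among unresponsive ones, the same in both arms, with responsive shares r1 and r2. The arms truly differ by (r1 − r2) × (a − b). If phone marks the responsive and form the unresponsive, the phone comparison gives a − a = 0 and the form comparison b − b = 0. Splitting by mode conditions on something that arises after randomisation, and here it hides the difference. Mode should be shown, but not used as the leading comparison.

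**The case against.** The strongest reply is that this is a secondary, qualitative outcome which already has a non-response remedy. The form exists precisely to reach caregivers who did not reply, and contact efforts is plural, so several emails may precede it. Caregiver burden and self-efficacy are measured separately and dietitians are interviewed too, so struggling families are not wholly invisible. The number of attempts and the reporting of response counts are details a journal article may leave to a fuller document. The text channel belongs to care: the article describes caregivers sending weights in, not research invitations going out, and using it could affect candour and burden.

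Much of this stands. The weakness is the single channel, not a single attempt, and the form may recover many caregivers. Stopping contact ends only the interview request, not trial participation. What does not fall away is the rule itself: the article states it from first contact to last, so the choice of channel is fixed and not merely left out. Burden, self-efficacy and clinician views do not replace what caregivers say about acceptability.

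Two stronger readings are tempting. A reader might infer that acceptability will be overstated by some definite amount, or that a real arm difference will vanish. That needs response rates the article does not give, and its extreme case requires that nobody completes the form. A reader might also infer that forms bring out fewer difficulties than phone calls. Nothing in the article supports that, and criticism could be franker on a form than to a clinic interviewer. That a form involves no probing is itself an inference from its being self-completed.

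**Conclusion.** The point holds as a minor design weakness with a cheap remedy. Before giving up on a caregiver, the rule uses only the channel that has already failed, for the only caregiver measure of an outcome named in the objective. The acceptability findings may therefore rest on the more responsive families. This assumes that responsiveness is related to how the approach is going, which is plausible but not shown. It also assumes that the text platform can carry an outgoing request, which the article does not state. No size or direction of bias, and no difference between arms, can be claimed from the documents. The primary weight outcome is not touched.

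**What to change.** In Caregiver Semistructured Interviews:
1. Before contact is discontinued, send the invitation and the form link, with at least one reminder, through the existing text or chat platform as well as by email.
2. Record for each caregiver whether the answer came by phone, by form or not at all, and report these counts by arm.
3. Keep the pooled by-arm summary of all respondents as the main comparison. Show mode descriptively only, because it arises after randomisation.

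The cost is a few more messages to caregivers, one variable and one small table. The downside is that the request travels through a channel also used for care. The message should therefore come from the research team and be identified as such.

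The Results expected data collection to end in November 2022. If contact has closed, step 1 is no longer possible. Steps 2 and 3 still are, provided that mode was logged or can be told from phone transcripts and form entries.

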#### Clinician Semistructured Interviews

A semistructured interview (Multimedia Appendix 3) with the RD interventionist will also be completed to assess the interventionists’ general experience with each approach. Interviews will be completed by a member of the Equip research team and completed remotely via Health Insurance Portability and Accountability Act–compliant Zoom platform.

